## Abstract

**Introduction:**

Low back pain (LBP) is the leading cause of years lived with disability in Nepal and elsewhere. Management of LBP that is evidence-based, easily accessible, cost-effective and culturally appropriate is desirable. The primary aim of this feasibility study is to determine if it is feasible to conduct a full randomised clinical trial evaluating the effectiveness of pain education as an intervention for individuals with LBP in Nepal, relative to guideline-based physiotherapy treatment. The findings of the study will inform the planning of a full clinical trial and if any modifications are required to the protocol before undertaking a full trial.

**Methods/analysis:**

This protocol describes an assessor-blinded feasibility clinical trial investigating feasibility of the pain education intervention in patients with non-specific LBP in a physiotherapy hospital in Kathmandu, Nepal. Forty patients with LBP will be randomly allocated to either pain education or guideline-based physiotherapy treatment (control). Outcomes will be assessed at baseline and at a 1 week post-treatment. The primary outcomes are related to feasibility, including: (1) participant willingness to participate in a randomised clinical trial, (2) feasibility of assessor blinding, (3) eligibility and recruitment rates, (4) acceptability of screening procedures and random allocation, (5) possible contamination between the groups, (6) intervention credibility, (7) intervention adherence, (8) treatment satisfaction and (9) difficulty in understanding the interventions being provided.

**Ethics/dissemination:**

The protocol was approved by Nepal Health Research Council (NHRC; registration number: 422/2017) and University of Otago Human Ethics Committee for Health (registration number: H17/157). The results of the study will be presented at national and international conferences and published in a peer-reviewed journal.

**Trial registration number:**

NCT03387228; Pre-results.

Strengths and limitations of this studyAssessor and statistician will be blinded to group allocation of the participants.Therapist and patient blinding is not possible in this study because of the nature of the treatments provided.Conclusions regarding the effectiveness of the intervention cannot be made because of the feasibility design of the current study.

## Introduction

Low back pain (LBP) is a highly prevalent health condition worldwide.^1 2^ It is the leading cause of disability^2^ and imposes huge economic burden to the society in both developed and developing countries.^3–6^ LBP is among the most common health conditions contributing to years lived with disability in Nepal.^2^ Although the prevalence of LBP is high in Nepal, ethnographic research has noted that LBP-related disability may be low in rural areas,^7^ perhaps due to the very low socioeconomic status of individuals living in rural Nepal, which forces them to keep working despite the presence of pain. Consistent with this idea, another study highlighted that 80% of people with chronic pain in Nepal continue to work.^6^ However, it is alarming that number of spine surgeries for spinal pain has been increasing in Nepal over the years,^8^ despite lack of evidence supporting efficacy for this treatment.^1 9^

### Interventions for management of LBP

Many interventions have been investigated for the management of LBP. These include surgery,^10 11^ pharmacotherapy,^12–17^ exercises,^18–20^ advice for self-management including advice to remain physically active^11^ and psychological therapies.^21 22^ As alluded to earlier, biomedically focused interventions such as surgery and pharmacotherapy are not recommended for a non-specific LBP as the evidence does not support their effectiveness.^1 14^ Moreover, they are associated with significant risks for adverse events and are costly.^5^

Clinical practice guidelines for LBP recommend self-management including reassurance, education and advice to remain active as the first line of care that should be provided to all the patients with LBP. Superficial heat and manual therapy (massage/manipulative therapy) are recommended for acute LBP, whereas exercise and psychological therapies are recommended for chronic LBP.^23–25^

### Pain education for LBP

Patient education for LBP that has been investigated in randomised controlled trials is basically of two types: biomedical education and pain biology education.^26^ The first refers to educating patients about vertebral anatomy and pathoanatomy of the spine, which has been shown to be ineffective and may even have negative effects on LBP outcomes.^26^ However, the second type of education—pain biology education (hereafter called as ‘pain education’)—has been shown to have positive effects on both pain and disability.^27 28^ Pain education is structured education programme with specific aims and objectives.^29^ This intervention has a list of target key concepts to be delivered and includes the curriculum contents to deliver the key concepts using up-to-date pain science knowledge, stories and metaphors.

It has been previously hypothesised that this type of education programme using metaphors and stories may be an effective intervention in Nepalese with chronic pain.^30^ However, the pain education materials that have been developed in western cultures are not necessarily valid and equally effective in reducing pain and disability in non-western cultures. Therefore, when developing pain education materials in a newer language or culture, (significant) cultural adaptations of the education materials may be required to make it suitable for the target population, as culturally inappropriate education may not produce desirable results.

Therefore, in order to evaluate the effectiveness of pain education in individuals with non-specific LBP from Nepal, culturally appropriate pain education materials should first be developed for Nepal, specifically. However, it is possible that the adaptations made could potentially reduce its effectiveness. Thus, before testing the adapted pain education in a full clinical trial, a feasibility study is needed in order to determine if a full clinical trial based on the adapted intervention is warranted, or if additional modifications may be needed prior to performing the full trial.

### Why the feasibility trial?

We propose a feasibility trial because: (1) the intervention (ie, pain education) will need significant cultural adaptation, although it has been evaluated for efficacy previously in other languages and western cultures; (2) the adapted intervention has never been investigated for its efficacy or effectiveness before; (3) the population in question (individuals with extremely low socioeconomic status and educational attainment in Nepal) is unique; and (4) a high-quality clinical trial in individuals with LBP has not been conducted in Nepal to our knowledge, and we therefore do not know if a full trial is feasible. The findings from the proposed feasibility study will inform the planning and design of a full trial, if the results indicate that a full trial is warranted.

The results of the full trial will have significant clinical implications for the management of LBP in Nepal and similar cultures, providing empirical evidence if pain education is a viable treatment for the management of LBP, and if it is effective in reducing pain, disability and emotional distress.

### Aims and objectives

The primary aim of the study is to evaluate the feasibility of a full randomised clinical trial (RCT) for assessing the effects of pain education as an intervention for patients with LBP of any duration in a physiotherapy facility in Nepal after developing culturally appropriate, evidence-based pain education materials. The primary objectives of the study are related to feasibility of an RCT, specifically: (1) willingness to participate in an RCT, (2) feasibility of assessor blinding, (3) eligibility and recruitment rates, (4) acceptability of screening procedures and random allocation, (5) possible contamination between the groups, (6) intervention credibility for patients with LBP, (7) intervention adherence, (8) treatment satisfaction and (9) difficulty in understanding the intervention being provided.

## Methods and analysis

### Study design and setting

This is a feasibility study that is being performed to determine if a full RCT can be successfully conducted using the procedures and protocol of the feasibility study, or if modifications of the protocol are needed prior to conducting the full trial. The study findings will inform the design of the full trial, if the trial is found to be feasible.^31^

The definition of a feasibility study highlights the question, ‘*Can this study be done?*’. The Standard Protocol Items: Recommendations for Interventional Trials (SPIRIT) statement,^32^ the Consolidated Standards of Reporting Trials statement extension to pilot and feasibility randomised trial^31^ were followed in the planning of the study and reporting of the protocol.

The study will be an assessor-blinded, two-arm, feasibility RCT. The study is registered in Clinicaltrials.gov (trial registration number: NCT03387228). The study will be conducted in the Sahara Physiotherapy Hospital, Kathmandu, Nepal.

### Overview of the study

Advertisement of the trial will be made in social media, and all the patients with LBP presenting at the study site will be invited to participate. Interested candidates will be screened for eligibility. Eligible patients with non-specific LBP will then be enrolled in the trial and be randomly assigned to one of the two study groups. All the participants in the experimental group will receive pain education and those in the control group (CG) will receive guideline-based physiotherapy treatment. All the participants will be assessed at baseline and 1 week following treatment. Details describing the schedule of enrolment, interventions and assessment are presented in table 1, in the manner recommended by SPIRIT checklist.^32^

**Table 1 T1:** Schedule of enrolment, assessment and interventions

Timepoint	Study period				
	Enrolment	Allocation	Post allocation		Final Assessment
	−T_1_	T_0_	T_1_	T_2_	T_3_
Enrolment					
Eligibility screening	X				
Explain study procedure/provide participant information sheets	X				
Informed consent	X				
Random treatment allocation		X			
Intervention					
Experimental intervention (PEG)				X	
Control group (CG)				X	
Assessment					
Baseline descriptive variables					
Sociodemographic information (age, sex, address, occupation, religion and ethnicity)			X		
History					
Pain history (site of pain, duration of pain, continuous or intermittent pain, aggravating and relieving factors)			X		
Comorbidities			X		
Feasibility					
Willingness to participate in a randomised controlled trial	X				
Acceptability of random allocation to one of the two groups	X				
Acceptability of intervention session (one session in a week with home treatment programme throughout the week)	X				
Feasibility of blinding the assessor*					X
Eligibility and recruitment rates	X				
Acceptability of screening procedures*					W
Understanding possible contamination between the groups					X
Evaluating the credibility of the intervention			X		X
Adherence to intervention					X
Treatment satisfaction					X
Difficulty in understanding the treatments					X
Secondary outcomes					
PROMIS Pain interference			X		X
PROMIS Pain intensity			X		X
Quality of life			X		X
PROMIS Sleep disturbance			X		X
PROMIS Depression			X		X
GROC			–		X
PCS			X		X
CD-RISC-10			X		X

*Assessed by the therapist providing intervention; all other outcomes are assessed by the blinded outcome assessor.

*CD-RISC-10*, 10-item Connor-Davidson Resilience Scale; GROC, Global Rating of Change; PCS, Pain Catastrophizing Scale; *PROMIS*, Patient-Reported Outcome Measurement Information System; *T_1_*, enrolment time; *T_0_*, allocation time; *T_1_*, baseline assessment (before treatment); *T_2_*, during treatment; *T_3_*, 1 week post-treatment; *W*, assessment at the end of every week on Fridays.

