### Group allocation, randomisation and blinding

Random number sequence, in random blocks of 4 and 6, will be generated using www.randomization.com, by a researcher ([name]) who is not involved in recruitment process. Allocation concealment will be performed using opaque, sealed envelopes. The participants will be allocated to one of the two groups by a hospital staff member who is not the assessor. The two groups will be: pain education group (PEG) and CG.

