4	Acceptability of screening procedures	The lead researcher will interview the physiotherapist(s) screening the potential participants for eligibility by asking the following open-ended question at the end of every week, ‘*Were there any difficulties or challenges in screening and recruiting the participants the past week?*’ The responses will be recorded as ‘Yes’ or ‘No’. If the answer to this question is ‘Yes’, the lead researcher will ask the following open-ended question, ‘*What were the difficulties and challenges?*’. Responses will be written down verbatim. Additionally, the outcome assessor will complete a form every time he or she encounters a difficulty or a challenge during screening. Outcome assessors will also be asked about their recommendations for overcoming any challenges that they identify. Time taken to complete the questionnaires will be recorded.	The frequency of difficulties or challenges will be counted. The difficulties and challenges will be noted, categorised if possible, and reported. Results will be used to improve the screening procedure in the full trial in future, and therapists’ recommendations will be considered.
5	Acceptability of random allocation to a treatment group	Outcome assessor will ask the participants if random allocation to one of the two treatment groups is acceptable to the participants. Responses will be recorded as ‘Acceptable’, ‘Not acceptable’ or ‘No preference’.	The frequencies of each response will be computed separately for each treatment condition.

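### Table 1 places the patient-reported baseline after random allocation although patients are unblinded, and Table 2 splits by arm an acceptability answer that Table 1 takes before allocation

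*Protocol article*

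**What the plan says.** Table 1 in the protocol article (Overview of the study) has columns for enrolment (−T1), allocation (T0), baseline (T1), treatment (T2) and final assessment (T3). T1 and T2 stand under the heading "Post allocation", and the legend confirms the order: "T_0_*, allocation time; *T_1_*, baseline assessment (before treatment". The row "Random treatment allocation" is marked at T0. The rows from "PROMIS Pain interference" down to the resilience scale, apart from the global rating of change, are marked at T1 and T3 only. Demographics and pain history are marked at T1.

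The text of the same section gives a matching order: "Eligible patients with non-specific LBP will then be enrolled in the trial and be randomly assigned to one of the two study groups". On concealment, Group allocation, randomisation and blinding specifies sealed envelopes and adds: "The participants will be allocated to one of the two groups by a hospital staff member who is not the assessor". The strengths and limitations box states: "Therapist and patient blinding is not possible in this study because of the nature of the treatments provided".

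Acceptability of random allocation is marked in Table 1 at enrolment only. Table 2, item 5 has the outcome assessor ask the question, gives no time point, and sets the analysis: "The frequencies of each response will be computed separately for each treatment condition".

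**The concern.** A baseline is protected from allocation only if it is taken before the participant can know the group. Here the patient is unblinded and every outcome is self-reported at interview, so expectation or disappointment about the assigned arm could colour the starting score. The Data analysis plan reports between-group differences in change, which would absorb any such shift.

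Two further things are at stake. Under the footnote to Table 1, the blinded outcome assessor conducts the T1 interview, so a patient who knows the group may reveal it. Assessor blinding is a primary feasibility objective and a progression criterion in Table 4. And a participant who leaves between T0 and T1 would have no scheduled baseline, so such losses could not be described.

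The acceptability item has the reverse problem: it is answered before any arm exists but reported as if it belonged to an arm.

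**Working it through.** The article states no figure that bears on this point. The check is a reading of the tables against each other, with two short derivations.

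**1. Order of events**

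| Item | Where marked in Table 1 |
|---|---|
| Consent; acceptability of random allocation | −T1 |
| Random allocation | T0 |
| Demographics, pain history, comorbidities | T1 |
| Pain interference, pain intensity, quality of life, sleep, depression, catastrophising, resilience (7 measures) | T1 and T3 |
| Credibility | T1 and T3 |
| Treatment | T2 |

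The legend's remark that T1 precedes treatment places it ahead of T2. It does not move it ahead of T0. One average-pain rating is needed for eligibility at −T1, but the baseline scores themselves are scheduled at T1.

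**2. Is the group known at T1?** The article does not say when the participant is told. Three facts point to yes: allocation has happened, patients are not blinded, and Table 2, item 7 asks credibility questions at baseline that refer to the treatment and are adapted to each condition. Such questions make sense only if the respondent knows the treatment. This is a strong inference, not a stated fact.

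**3. Effect on the difference in change.** Let D = (mean change, pain education) − (mean change, control). Suppose knowing the group shifts the baseline mean by a in the pain education arm and by b in the control arm, and a fraction f of each shift is still present at T3. Then D moves by (f·a − a) − (f·b − b) = −(1 − f)(a − b).
- Shift in one arm only (b = 0), gone by T3 (f = 0): D moves by −a, the full shift in the opposite direction.
- Shift fully persistent (f = 1), or equal in both arms (a = b): D does not move.

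The article gives none of a, b or f, so no number follows.

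**4. Acceptability by arm.** The answer is given at −T1 and the arm is drawn at random at T0, independently of the answer. Among those randomised, the probability of each response is the same in both arms, so the expected difference is 0 and any observed difference is chance. A person who refuses randomisation at −T1 never receives an arm and cannot appear in a by-arm table.

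**The case against.** The strongest reply is that the article never says participants know their group at T1. Envelopes are sealed, a staff member other than the assessor allocates, and blinding is called impossible because of the treatments, which start only at T2. The credibility wording is also awkward evidence, since at T1 no treatment has yet been given. This stands to the extent that knowledge at T1 is inferred. It does not remove the point, because nothing in the schedule prevents disclosure before baseline.

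Second, little in this trial depends on the effect sizes. The Data analysis plan excludes efficacy testing and bars the effect sizes from sample-size and progression decisions, and no Table 4 criterion uses change in a secondary outcome. That stands and limits the severity. Participants are also told that both treatments are thought effective, which may reduce any shift.

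A reader might go further and infer that the baseline is spoiled as a covariate, or that the bias can be sized against a standard error. Neither is supported. No covariate adjustment is described. The article gives no expected shift and no correlation between baseline and follow-up, and its SD of 10 is a normative value for the four PROMIS scales only, not for all seven measures.

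Third, Table 2, item 5 asks about random allocation as a process, so it is not at fault for failing to measure satisfaction with the arm received. That is fair. The defect is only that a pre-allocation answer is tabulated by arm.

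**Conclusion.** Both points hold, at moderate weight.

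The seven patient-reported baselines are scheduled after allocation, in a trial with unblinded patients, and no part of the article corrects the order. The schedule permits, and probably entails, baseline answers given with knowledge of the group. Whether a shift occurs, and how large it is, cannot be determined from the article. What matters is the reported effect sizes, the assessor-blinding criterion, and carry-over: the study is meant to test procedures that the full trial may use unchanged, and there the change scores will count. The conclusion assumes that participants learn the group at or soon after T0.

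The by-arm acceptability table is uninformative by construction, and Tables 1 and 2 need to be reconciled.

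**What to change.** - **Baseline.** Collect demographics, pain history and the seven patient-reported measures after consent and before the envelope is opened, and re-order Table 1 accordingly.
- **Credibility.** Leave only these five items after allocation. Have them asked by someone other than the blinded assessor, for example the staff member who allocates and so already knows the group.
- **Acceptability of random allocation.** Report the enrolment answer once, for everyone asked, including those who refuse. If a by-arm figure is wanted, ask again after allocation, either through existing staff other than the blinded assessor or after the assessor's group guess has been recorded. A question about the arm received, put by the blinded assessor before that guess, would invite disclosure.

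The cost is a re-ordering within the same visit, a few minutes of another staff member's time for the credibility items, and one optional repeated question. No extra visit is needed.

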### Participants

Patients with non-specific LBP seeking rehabilitative services at Sahara Physiotherapy Hospital will be invited to participate. Interested patients will be screened by a research assistant (physiotherapist by training) involved in the research.

#### Inclusion criteria

Non-specific LBP (LBP other than those excluded, see exclusion criteria below) of any duration with pain primarily localised between T12 and gluteal folds, in patients aged 18 years or older, with average pain intensity reported as moderate, severe, or very severe on a Patient-Reported Outcome Measurement Information System (PROMIS) five-point PROMIS Pain Intensity Short-form Scale^33^ over the past week, and who is a Nepalese and is able to understand and speak Nepali fluently will be included in the study.

#### Exclusion criteria

Participants with likely specific causes of LBP will be excluded using a triage procedure as suggested by Bardin and colleagues.^34^ This includes exclusion of participants having history of prolonged use of corticosteroid, history of malignancy, recent history of fever or chills, history of other diseases associated with compromise in immune system, history of recent spinal surgery or dental procedures, recent history of trauma to spine or a fracture of a spine, history of bladder and bowel dysfunction, history of perineal or saddle anaesthesia and history of weakness of lower extremity or loss of sensation in lower extremity. Additionally, current pregnancy and history of diagnosed mental health conditions that would limit adherence to the trial procedures will be excluded.

### Sample size

For a feasibility study, it is inappropriate to calculate sample size based on desired statistical power to detect a treatment effect,^35^ because the primary aim of the study is to assess if a full trial can or should be conducted. Feasibility outcomes are descriptive in nature; therefore, inferential statistics regarding treatment effects will not be computed. To achieve the primary objectives related to feasibility outcomes, the research team estimated that 40 participants would be adequate.^36^ Twenty patients will be randomly allocated to each treatment condition.

